*A priori* sample size and power analyses using The Shiny CRT Calculator [55] for the CRCT with pre-post assessment was conducted [56] with a critical significant level of 5%, a power of 80%, an expected moderate effect size of ƒ = 0.25, and an assumed intra-class correlation coefficient of .05. Previous ICC-T trials in Tanzanian secondary schools revealed moderate to large effects on student-reported and teacher-reported violence by teachers, respectively [3, 4, 39, 53]. Assuming no dropout at the school level and accounting for potential dropout on the participant level of 25%, and eight clusters per arm, 25 to 28 participants within a cluster would result in sufficient power. To account for parents’ response rates that are expected to be lower than 100%, parents from 45 randomly selected students will be invited to participate. Based on an expected approximated 85% response rate of invited mothers and 65% of invited fathers, 38 mothers and 29 fathers are assumed to participate in the study. In addition, 25 teacher per school will be included in the present study. This results in a sample size of 720 students, 608 mothers, 464 fathers and 400 teachers across 16 schools. Based on these assumptions, an *a priori *power of ß = .94 for students, for mothers ß = .90, for fathers ß = .82, and ß = .76 for teachers was calculated.

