### Outcomes

Quantitative data will be collected to investigate the effects of ICC-T and ICC-P on the teachers’ and parents’ use of violence against children in home and school. As primary quantitative outcome, violence by teachers in school and by parents at home will be assessed. The secondary quantitative outcome measures include parents’ and teachers’ favorable attitudes towards violence, children’s mental health problems, children’s quality of life, peer violence experienced by children, parent–child relationship and teacher–child relationship, perceived stress of all participants, school climate experienced by teachers, teachers’ self-efficacy, teachers’ decision making, teachers’ and parents’ normative beliefs about violence, and intimate partner violence experienced by female parents. All primary and secondary quantitative outcomes will be collected at baseline and follow-up data assessment. In addition, socio-demographic data on participants’ age, gender, and living situation will be assessed. Apart from this, children will be asked to identify the two most caring persons for them personally and parents and teachers will be asked on their household earnings.

Qualitative information will be collected to complement the quantitative data with FGDs and in-depth interviews for process evaluation and qualitative end-line evaluation. A process evaluation will be conducted to assess the quality and fidelity of the implementation of the intervention, participants’ engagement with the intervention, and whether the intervention achieved its goals in terms of its primary and secondary quantitative outcomes. The FDGs will assess the parents’ and teachers’ experiences with and thoughts on the intervention. The in-depth interview will assess parents’ and teachers’ perceived improvement of violence reduction. For qualitative information on process evaluation, standardized evaluation as well as reflection forms will assess the staff members’ experiences with conducting the intervention.

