#### Primary quantitative outcomes

##### Parental violence

The use of emotional and physical violence by parents against children at home will be measured with adapted versions of the Conflict Tactics Scale (CTS) [3, 63, 64], on the one hand by children’s self-reported violence experiences and on the other hand by parents’ self-report on the use of violence. For the present study, the CTS will include 9 items on experienced physical violence, 7 items on experienced emotional violence, and 5 items on emotional maltreatment. The items will be answered on a 7-point Likert scale ranging from 0 (this has never happened in the past week) to 6 (not past week, but before). CTS-scores on emotional and physical violence will be derived by summing up the respective item scores, whereby higher scores indicate higher levels of parental violence. A previous study in Tanzania assessed parental violence with the adapted CTS versions and revealed good psychometric properties [53].

In addition, during the quantitative interview 4 CTS-items will be body mapped by asking the children where on their body they experienced the emotional (shout & call dumps) and physical (hit & slap) violent act by parents. The affected body parts will be documented on a sheet of paper with a body-icon. Promising results for body mapping have been shown for trauma research in the context of refugees [65].

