##### Teachers’ violence

An adapted version of the CTS [3, 63, 64] will be used to assess the emotional and physical violence by teachers at school, captured through both children’s and teachers’ self-reports. The CTS will include 9 items on physical violence, 7 items on emotional violence. For children’s report, 2 additional purpose-built items on witnessed violence by teachers will be assessed. The teacher version uses the same answer scale and scoring as the CTS versions for parental violence (c.f., for more details outcome description about parental violence). Previous studies in East Africa assessing teachers’ violence revealed acceptable psychometric properties [14, 66, 67].

In addition, during the quantitative interview 4 CTS-items will be body mapped by asking the children where on their body they experienced the emotional (shout & threaten) and physical (hit & pinch) violent act by teachers. The affected body parts will be documented on a sheet of paper with a body-icon. Promising results for body mapping have been shown for trauma research in the context of refugees [65].

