## Data analyses

### Quantitative outcomes

To statistically investigate the study’s main research question whether ICC-T and ICC-P have a decreasing effect on teachers’ and parents’ use of violence against children in home and school settings, interaction effects of time*intervention will be modeled on the primary outcomes of teachers’ and parents’ violence use against children reported by teachers, parents and children respectively in mixed models for repeated measures accounting for cluster effects of participants’ nested in school. Secondary outcomes will be analyzed for potential time*intervention with mixed models. In case of significantly (*p* < 0.05) zero-inflated outcomes, model approaches for non-normally distributed data (e.g., Poisson, negative binomial) will be used. In case of unstable models due to potential outliers, variables will be winsorized (quantiles 5% & 95%) for model robustness. In case of missing data at random, multiple imputation methods will be used. Models will be corrected for multiple testing. In addition to the main inferential analyses, the prevalence of maltreatment and violence in different settings as well as children’s mental health and well-being from baseline assessment data will be captured based on descriptive statistics. Results will be presented including appropriate effects sizes and with a measure of precision (95% confidence intervals). Effect size of η^2^ ≥ 0.01, η^2^ ≥ 0.06, η^2^ ≥ 0.14 will be considered representing a small, moderate, and large effect, respectively [96].

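### Power is stated at an uncorrected 5%, but the plan promises a multiplicity correction over at least four primary tests, so the printed powers overstate those of the corrected tests

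*Protocol article*

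**What the plan says.** In the Protocol article, the sample-size paragraph under Participants describes a calculation "with a critical significant level of 5%, a power of 80" per cent. Its other inputs are "an expected moderate effect size of ƒ = 0.25", "an assumed intra-class correlation coefficient of .05", and a design "accounting for potential dropout on the participant level of 25%, and eight clusters per arm". It reports power of .94 for students, .90 for mothers, .82 for fathers and .76 for teachers. No multiplicity adjustment is mentioned there.

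The Outcomes section defines the primary outcome broadly: "As primary quantitative outcome, violence by teachers in school and by parents at home will be assessed". Each of the two targets has two reporters. Under Parental violence, the data come from children's "self-reported violence experiences and on the other hand by" the parents' own report. Under Teachers' violence, an adapted Conflict Tactics Scale "will be used to assess the emotional and physical violence by teachers at school", answered by children and by teachers. The Parental violence section derives emotional and physical scores by summing their respective items, and the teacher version uses the same scoring.

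Data analyses, Quantitative outcomes, models time-by-intervention interactions for these outcomes as reported by teachers, parents and children, and then states: "Models will be corrected for multiple testing". It does not say which tests form the family or which method applies. No primary comparison is placed first.

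**The concern.** The two statements cannot both describe the same tests. If the primary tests are corrected, they do not all run at the 5% on which the four powers rest. A reader who takes .94/.90/.82/.76 as the chance of detecting the planned effect in the confirmatory analysis will be too optimistic.

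This matters most where there is least margin. Fathers are planned at .82 and teachers at .76, against a target of .80. These groups supply adult self-reports that the analysis section treats as primary. If the family and method are chosen only after follow-up data are seen, that choice could also change which primary results count as positive.

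**Working it through.** **Inputs.** All come from the sample-size paragraph: 5% level, 80% target, f = 0.25, intra-class correlation .05, eight schools per arm, and 25% participant dropout. Participants per school are 45 students, 38 mothers, 29 fathers and 25 teachers. The stated powers are .94/.90/.82/.76. Two-sided testing is assumed, because sidedness is not stated.

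**Step 1: the plan's own figures.** With a follow-up-only comparison, the effective number per arm is 8m / (1 + (m − 1) × .05). For students this is 360 / 3.2 = 112.5. With d = 0.5 (the usual conversion of f = 0.25), power is Φ(0.5 × √(112.5/2) − 1.96) = Φ(1.79) = .963. All four groups give .963/.955/.935/.921, or .947/.934/.904/.883 after 25% dropout. With d = 0.25, power is only about .31 to .47. The stated inputs alone therefore do not return the four figures. A pre-post calculation also needs cluster and individual autocorrelations, which are not given. One such set (d = 0.25, difference-in-differences, 25% dropout, cluster autocorrelation 1.0, individual autocorrelation 0.65) gives .945/.905/.816/.756, close to the stated values. The mismatch does not show the stated powers to be wrong, and they are taken as given below.

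**Step 2: number of primary tests.** Two targets × two reporters = 4. If physical and emotional scores are tested separately, 4 × 2 = 8. If mothers and fathers are also modelled separately, as they were sized, there are 4 child-report, 2 mother, 2 father and 2 teacher tests = 10.

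**Step 3: implied signal.** For each group, noncentrality = z(power) + 1.960. For students this is 1.555 + 1.960 = 3.515. The others are 3.242 (mothers), 2.875 (fathers) and 2.666 (teachers).

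**Step 4: Bonferroni over k tests.** Power = Φ(noncentrality − z(1 − .05/2k)).
- Students, k = 8: Φ(3.515 − 2.734) = Φ(0.781) = .78.
- Fathers, k = 2: Φ(2.875 − 2.241) = Φ(0.634) = .74.

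**Step 5: Holm and Benjamini-Hochberg over eight.** These were simulated with 100,000 runs per setting. All effects were real, test correlation was 0 or 0.5, and both a normal and a 14-df t reference were used. The family was four child-report, two parent and two teacher tests, with the parent tests set at the mothers' or at the fathers' power. The ranges span those settings.

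| Rule | Students | Mothers | Fathers | Teachers |
|---|---|---|---|---|
| Stated, 5% per test | .94 | .90 | .82 | .76 |
| Bonferroni, 2 tests | .90 | .84 | .74 | .665 |
| Bonferroni, 4 tests | .845 | .77 | .65 | .57 |
| Bonferroni, 8 tests | .78 | .69 | .56 | .47 |
| Bonferroni, 10 tests | .76 | .67 | .53 | .44 |
| Holm, 8 tests | .81–.89 | .76–.83 | .66–.71 | .60–.66 |
| Benjamini-Hochberg, 8 tests | .91–.93 | .87–.89 | .79–.80 | .73–.75 |

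**Step 6: sensitivity to the small number of schools.** Repeating steps 3 and 4 with a t reference on 14 df (16 schools − 2) gives .80/.73/.60/.52 for four Bonferroni tests and .71/.61/.48/.40 for eight.

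**The case against.** The strongest reply is that the method, family and split of alpha are normally left to the statistical analysis plan, which is not shown, and that the article does commit to a correction. This stands as far as missing detail goes, and the absence of that detail is not the point here. The power statement and the promise to correct are both printed in the article, and they do not match.

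A reader might infer that no group keeps 80% power. The document does not support that. It follows only from a single-step split over about seven or more tests: with Bonferroni, students are at .81 with six tests and .795 with seven. Students keep 80% under Holm over eight, under Benjamini-Hochberg, or in a family of four. Mothers keep it under Benjamini-Hochberg and may under Holm. Teachers start at .76, so they have no 80% to lose.

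Some other readings also go too far:
- Eight tests is a fair reading of the scoring text, but the article does not state that count. If the physical and emotional scores are combined, the minimum is four.
- Eight independent uncorrected tests would have a familywise error of 1 − .95^8 = 34%, but that describes an analysis the plan rejects.
- No further deduction for loss should be made from the stated powers. The paragraph says 25% dropout was accounted for.
- Demoting adult self-reports because trained adults are unmasked is a design preference. The Procedures section says participants will be unmasked at follow-up and does not exempt children.

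**Conclusion.** The point holds in a limited form: the four printed powers apply to uncorrected tests and overstate the power of the corrected ones. The direction is clear, because a result that survives any of the corrections examined must also have p ≤ .05, so corrected power cannot exceed the stated figure. A fixed testing order would spare the first test, but the plan names no order.

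The size depends on the unnamed family and method. It runs from a loss of a few points under Benjamini-Hochberg over eight to .78/.69/.56/.47 under Bonferroni over eight. Teachers are below target in every case, including before correction. Fathers are below it under Bonferroni with two or more tests and under Holm over eight, and sit at about .79 to .80 under Benjamini-Hochberg.

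These figures rest on the stated powers being right, on two-sided tests and, for the Bonferroni rows of the table, on a normal approximation. The Holm and Benjamini-Hochberg ranges also assume that every effect is real.

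**What to change.** Before follow-up data are analysed:
1. List the primary tests, saying whether physical and emotional scores, and mothers and fathers, are tested separately.
2. Name the correction method, for example Holm over that list.
3. Restate power for each group at the corresponding adjusted level. Under Holm that level depends on the other p-values, so give either the first-step value (.05/k, the Bonferroni row) as a lower bound or a simulated value with its assumptions.
4. Say plainly which groups fall below 80% under the chosen rule. Teachers will, and fathers will under most of the rules examined.

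The investigators could instead name two child-reported co-primary outcomes, one for violence by teachers and one for violence by parents. Student power would then be about .90 at alpha .025. That is an option, not a required correction, and it would take confirmatory status from the adult self-reports.

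The cost is wording in the protocol and analysis plan. No extra participants are needed. The downside is that the published powers become less favourable.

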#### Qualitative information

FGDs and in-depth interviews will be recorded, transcribed verbatim, and translated to English. Transcripts will be analyzed by two team members ([name]) using qualitative content analysis in Atlas.ti.

## Discussion

Several studies suggest that violence against children is associated with lower quality in the child–adult relationship, negative mental health outcomes, and behavioral and emotional problems that begin in childhood and are very likely to persist throughout adolescence and adulthood [7–11, 32]. Studies show that nine out of ten countries with the highest rates of violent discipline use against children are in Africa [2, 6].

Despite attempts to legally banning violence against children in various African countries, in Tanzania violent discipline is still permitted [97–99]. Preventive interventions are promising to reduce violence against children by directly targeting the structural engines of school and family. In particular, the ICC program offers parents and teachers a basic training in the essential interaction competencies in interacting with children [41]. The intervention focuses on non-violent interaction strategies and on encouraging warm, sensitive, and reliable adult–child relationships. ICC enhances awareness for violence and its negative consequences and reduces favorable attitudes towards as well as the use of violence against children. Thus, to prevent violence, ICC is a bottom-up approach that targets the schools and families as engine to effectively reduce violence against children [35].

In the present project, ICC-T as well as ICC-P will be delivered together within a school-based approach. With this unique approach of combining ICC-T and ICC-P, it is expected for the present research project that the intervention will especially foster the children’s consistent experience of non-violent discipline behaviors by their teachers and parents. By reducing violence against children, we aim to contribute to the decrease of children’s risk of adverse mental health outcomes that are associated with violence exposure.

To investigate the effectiveness of ICC-T and ICC-P on shared school-ground, a CRCT with 16 schools will be conducted. CRCT with pre-post intervention assessment allow for strong tests to investigate how violence use and favorable attitudes towards violence might change over a short period of time within participants that received the intervention as well as between participants comparing intervention and control condition. The use of violence assessed pre- and post-intervention will help to understand temporal changes in violence use and experience over short time. Besides these strengths of the present design, extended and multiple occasions of measurement may be helpful to understand the sustainable effectiveness of the intervention. If, as in the present study, the initial effectiveness after three months is confirmed, investigating the long term effectiveness will be highly promising. Especially well-being and health as downstream effects of violence reduction are promising to investigate in long term settings.

Sixteen schools will be selected from one region (Morogoro) in Eastern Tanzania. Conducting the present project with participants specifically from the urban districts of Morogoro, it might be possible that diverse nuances in societally influenced beliefs on violence use might differ between regions of Tanzanian. If the combination of ICC-T and ICC-P reveals effective reduction of violence use against children larger studies across various Tanzanian regions and even across various countries would be important.

The present project is aiming to reduce children’s violence exposure by educating teachers and parents on non-violent interaction competencies. Through this, the present project contributes to the efforts of Pan-African [100] and United Nations Conventions on the Rights of the Child [1] to end all violence against children.

## Data Availability

Anonymized quantitative and qualitative data will be made publicly available without expiration date in the online repository Open Science Framework (OSF) [101].

## Abbreviations

CRCTs: Cluster-randomized control trails
CTS: Conflict Tactics Scale
FGDs: Focus group discussions
ICC: Interaction Competencies with Children
ICC-T: Interaction Competencies with Children—for Teachers
ICC-P: Interaction Competencies with Children—for Parents
Km: Kilometers
MPVS: Multidimensional Peer Victimization Scale
No.: Number
OSF: Open Science Framework
PIML: People In My Life
PLH: Parenting for Lifelong Health
PSC-17-Y: Short version (17 item) of Pediatric Symptom Checklist – Youth Report
TIDieR: Template for Intervention Description and Replication
TUM: Technical University Munich
UN: United Nation
